## Eligibility criteria {10}

### Participant inclusion and exclusion criteria

To enroll in the study, school administrators will be invited to sign a memorandum of understanding (MoU) indicating their willingness to participate. The students from the participating schools will be informed about the study by a contact person from the school. Then, the project team will organize a session with students one week before implementation starts to describe the program in detail. All students aged 13 to 20 who express interest in joining the program will be eligible for the study, with no additional exclusion criteria applied.

The Shamiri intervention will be delivered by trained group facilitators, all lay providers with at least a high school degree, who will each lead the intervention for a group of 10 to 15 adolescents. Lay providers will be included if they live near Makueni or Machakos counties, are between the ages of 18 and 24, and graduated from a Kenyan secondary school. Applicants who meet these criteria will participate in 30-min interviews and will be selected based on their counseling or group facilitation skills and knowledge of common issues faced by Kenyan secondary school students. The recruitment and training of lay providers will closely mirror the procedures employed in previous trials of the Shamiri Intervention [17].

Recruiting local peers as lay providers has several advantages; the local lay providers are connected and well-versed in the culture of our target population and will thus be able to relate well to the target group. Furthermore, if the intervention again proves to be successful, one of the most efficient and cost-effective ways of scaling up will be through local lay providers.

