### Implementation {16c}

Once students have been given their group numbers, they will go to their assigned groups to meet their group leaders, who will then confirm that they are in the correct group. Once the participant’s settle in their groups, the group leader will direct the filling of an attendance sheet containing participant information—name, admission number, and form—then randomization will be complete. The specific groups and arms assigned will be maintained throughout the study.

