## Statistical methods

### Statistical methods for primary and secondary outcomes {20a}

Our data analysis plan will involve descriptive statistics, visualizations, and models of change over time. We will follow an intent-to-treat approach [41], analyzing all the study participants assigned to their intervention arm. Our findings will be summarized using tables and graphs.

For descriptive statistics, we will compute the frequencies and percentages of the demographic and clinical characteristics for the study participants at baseline by the intervention arm. To test for significant group differences in the sample characteristic variables, we will use *F*, *t*, and *χ*^2^ statistics [42].

Primary outcome variations across all the time points will be visualized using multiple plots. We will include line plots for depressive symptoms, anxiety symptoms, academic grades, well-being, and perceived social support for the Shamiri intervention per implementer and TAU control arm, visualizing scores before, during, and after the intervention and control condition.

We will build linear mixed effects models [43, 44] as part of the analysis to compare the outcomes of the two Shamiri intervention and the TAU control groups. These models will consider the hierarchical nature of the data, where participants are nested within organizational structures (participant in lay provider/group in school in county). The standard models will be random-intercept models; we will also test the inclusion of random slopes for individual differences. Some of the model elements (e.g., multiple levels of nesting and the random slope) may result in models that are too complex, unidentifiable, or overfit; in such a case, more parsimonious models will be selected.

The arm, time, and interaction between these two will be included in all the models as fixed effects. Other variables that will be included either in a fixed effect or in a random effect specification in the models are age, gender, lay provider, lay provider gender, school, and county. Baseline scores may also be included. Age will be included as a covariate as older adolescents in Kenya have been found to on average have increased psychosocial stress compared to younger adolescents which may heighten depressive and anxiety symptoms [12].

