Gender will be included because Kenyan adolescents have shown gender differences in internalizing problems [8, 12]. Female adolescents have previously reported higher anxiety and depression symptoms as compared to males. Past studies [8, 12] have shown that adolescents in lower-resource schools report higher depression and anxiety symptoms. Lastly, we will include details of lay providers like gender because we would like to explore if the gender of a lay provider affects the study participants.

A *p*-value less than 0.05 in the interaction between the time variable and the arm variable will be considered statistically significant. If the interaction is significant, we will look at the conditional mean difference between the arms at each time point from end point to follow-up. We will assess this and report marginal (predictive) means. If these differences are significant (*p* < 0.05) and the control has scores associated with less favorable outcomes, we will conclude there was improvement due to centralized or decentralized arm over time. If the interaction is not significant but the main effect of centralized or decentralized arm is, and the effect points to lower symptoms in the centralized or decentralized arms, we conclude there was improvement due to centralized or decentralized delivery.

Effect sizes (ESs) will be computed from the mean differences across the different time points for the arms. We will compare Cohen’s D for each outcome at baseline, midpoint, endpoint, and 1-month follow-up for the study participants in the Shamiri intervention arms and TAU control arm. Statistically significant Cohen’s *D* in the direction of less symptoms on average in the arms will reflect greater improvements for intervention compared to control.

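### The stated random-intercept model leaves group-to-group variation in change out of the arm-by-time test, so the test rejects too often if lay-provider groups diverge after baseline

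*Protocol article*

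**What the plan says.** All analysis statements are in the protocol article, section {20a}.

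- **Nesting.** The models are to reflect that "participants are nested within organizational structures (participant in lay provider/group in school in county".
- **Random effects.** "The standard models will be random-intercept models; we will also test the inclusion of random slopes for individual differences". If the model proves too complex, "in such a case, more parsimonious models will be selected".
- **Fixed effects.** "The arm, time, and interaction between these two will be included in all the models as fixed effects". Lay provider, school and county may enter as fixed or random terms, and baseline scores may be added. No term lets a group's or a lay provider's change over time vary.
- **Decision rule.** A p-value "less than 0.05 in the interaction between the time variable and the arm variable will be considered statistically significant". If it is significant, arm differences at endpoint and follow-up are examined and must also be significant, with control faring worse. If it is not, a significant arm main effect can still support a conclusion of improvement.

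The group structure is set elsewhere. The eligibility section describes lay providers "who will each lead the intervention for a group of 10 to 15 adolescents". Under Sequence generation {16a}, one ballot paper fixes both group and arm. Under Implementation {16c}, "The specific groups and arms assigned will be maintained throughout the study".

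**The concern.** Because the ballot forms the groups at random, they should differ little at baseline. Differences due to the lay provider or to the peers in the room can arise only after sessions start. That is variation between groups in change over time.

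The stated model has no place for it. A random intercept for group is the same at every visit, so it drops out of any within-group change and gives the arm-by-time contrast no protection. Individual random slopes are independent between members of the same group, so they cannot represent a shift that members share. Entering lay provider as a main effect has the same limit. The test can therefore reject because some groups changed more than others, even when the arms do not differ on average.

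The effect is largest for centralized versus decentralized, where both arms are grouped. Section {6b} calls that comparison the primary objective. Chance differences between lay providers could be read as a difference between implementers.

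**Working it through.** **The plan's own figure.** For this point it is the nominal 5%. Fitting the planned model (REML, participant and group intercepts) to null data with a group ICC of 0.05 that is constant at all visits, baseline included, gives 4.4-4.9% rejection. The test is sound in that case, and the problem is specific to a group effect that appears after baseline.

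**Inputs from the protocol.** Groups of 10 to 15; 1600 students in three equal arms; visits at 0, 2, 4 and 8 weeks; attrition of 30%, 30% and 40% at midpoint, endpoint and follow-up.

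**Assumptions.** Groups of 12, with 43 per active arm (516 students per arm); TAU ungrouped; categorical time, so the interaction has (3-1)(4-1) = 6 df; total variance about 1; within-student correlation 0.5 to 0.65; group effect loading 0, 0.5, 1, 1 over the four visits. The ICC is varied because the protocol gives none.

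**Closed form, baseline to endpoint.** The per-student change variance is 2(1 - rho), which is 1.0 at rho = 0.5 and 0.7 at rho = 0.65. With m students per group, the variance of an active arm's mean change is inflated by

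k = 1 + (m - 1) x ICC / [2(1 - rho)].

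The true SE divided by the model SE is sqrt(k) for active versus active and sqrt((k + 1)/2) for active versus TAU. The actual size of a nominal 5% test is 2 x [1 - Phi(1.96/ratio)].

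At ICC 0.05 and m = 12:

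- rho = 0.5: k = 1 + 11 x 0.05/1.0 = 1.55. The ratios are 1.24 (size 11.5%) and 1.13 (8.3%).
- rho = 0.65: k = 1 + 11 x 0.05/0.7 = 1.79. The ratios are 1.34 (14.2%) and 1.18 (9.7%).

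As a check at rho = 0.5, the true SE for active versus active is sqrt(2 x 1.55/516) = 0.078. Fitted mixed models with participant and group intercepts reported about 0.062.

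At ICC 0.05 with 30% loss, m = 12 x 0.7 = 8.4:

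- rho = 0.5: k = 1.37. The ratios are 1.17 (9.4%) and 1.09 (7.2%).
- rho = 0.65: k = 1.53. The ratios are 1.24 (11.3%) and 1.12 (8.1%).

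**Simulation, no attrition, 4000 null trials per scenario.**

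| Group ICC | 6-df interaction | Centralized vs decentralized | Active vs TAU |
|---|---|---|---|
| 0.01 | 6-7% | 7% | 6% |
| 0.02 | 7-8% | 8-9% | 7% |
| 0.05 | 10-13% | 12-15% | 8-10% |
| 0.10 | 17-21% | 18-23% | 12-15% |

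If the group effect halves by follow-up (ICC 0.05, rho = 0.5), the interaction test rejects 8% and the implementer contrast 12%.

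**Fitted planned model, ICC 0.05, TAU ungrouped, rho 0.5 to 0.7, linear or categorical time.** It rejects 9.7-15.6% without attrition and 7.9-12.7% with the planned attrition. A balanced simulation with groups of 8, roughly what attrition leaves, gives 7-9% for the interaction and 9-12% for the implementer contrast.

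**Does the missing term explain it?** With all three arms grouped, no attrition and ICC 0.05, adding individual slopes alone leaves 13-21%. Analysing group mean slopes in the same data, which allows for group-level change, gives 5.4-6.0%.

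**The case against.** A reader might infer that the trial's conclusions carry two to three times the nominal error, because every claim must first pass the interaction test. Section {20a} does not support that. A significant interaction must be followed by a significant contrast at endpoint or follow-up in the right direction, and a non-significant one leaves the main-effect route. Those level contrasts carry group-intercept variance, so they are partly protected. Simulating the whole rule without attrition gave false claims of improvement, for either active arm on one outcome, of 6.0-6.3% at ICC 0.05 against 4.2-4.3% at ICC 0, and 7.6-8.0% at ICC 0.10. At ICC 0.05 that is about 1.5 times the unclustered rate (6.3/4.3). This objection stands.

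Other limits also stand:

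- The size rests on an assumed ICC and correlation, and it shrinks under the attrition the plan itself expects.
- The rule for concluding improvement compares active arms with control. Section {20a} gives no conclusion rule for the implementer contrast, where inflation is largest. The hypothesis there is equal effectiveness, so false rejection would count against it, though intervals would still be too narrow.
- Academic performance is measured by school term, so the four-visit simulation does not carry over to all five primary outcomes.
- The planned multiple imputation was not simulated.

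Two objections only soften the point. Baseline scores may be included, and with baseline as a covariate and only post-baseline visits as outcomes the interaction rejects about 6-8% at ICC 0.05; but this is optional in the text. The plan does not forbid a group slope, and an unseen analysis plan might add one. Still, the article states its standard model, names slopes for individuals only, and lets complexity be reduced further.

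**Conclusion.** The concern holds for the model as stated. With random intercepts and at most individual slopes, the arm-by-time test and the change contrasts have standard errors that are too small whenever lay-provider groups diverge after baseline, which this design makes likely.

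The size depends on assumptions. At a post-baseline group ICC of 0.05 with TAU ungrouped and no attrition, a nominal 5% test rejects about 10-13% (interaction), 12-15% (centralized versus decentralized) and 8-10% (active versus TAU). With the planned attrition, the interaction rejects roughly 7-13% depending on the model, and the implementer contrast roughly 9-12%. At ICC 0.02 or below, the rates are about 6-9%. A group effect constant from baseline causes no inflation. These are error rates of individual tests; the final claim of improvement is inflated less.

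**What to change.** In section {20a}, pre-specify a group-by-time random effect for the two Shamiri arms, either a group slope or a group effect at each post-baseline visit. State that the parsimony rule may not remove it. If the model does not converge, use small-sample cluster-robust standard errors by group, treating each TAU student as a separate cluster. Base the interaction test and the endpoint and follow-up contrasts on that model.

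This takes a sentence or two and no new data. The cost is wider intervals: at ICC 0.05 without attrition, standard errors are about 24-34% larger for centralized versus decentralized and 13-18% larger for active versus TAU. With 8.4 students left per group, the ratios above give about 17-24% and 9-12%. If group variation in change proves negligible, little is lost.

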**Methods:**

In this three-arm trial, 1600 adolescents aged 13 to 20 years will be randomized to receive the Shamiri intervention from either the Shamiri Institute or an implementation partner or to be placed in the treatment as usual (TAU) control group. The implementation partner will be trained and supplied with protocols to ensure that the same procedures are followed by both implementors. Implementation activities will run concurrently for both implementors. The Shamiri intervention will be delivered by trained lay providers to groups of 10–15 adolescents over four weekly sessions which will take place in secondary schools in Machakos and Makueni counties in Kenya. The TAU group will receive the usual care offered by their respective schools. Outcomes will be assessed at baseline, midpoint (2 weeks), endpoint (4 weeks), and 1 month follow-up. The analysis will be based on an intent-to-treat approach. Mixed effects models will be used to assess trajectories over time of the primary outcomes (anxiety and depressive symptoms, mental well-being, perceived social support, and academic performance) and secondary outcomes for the intervention groups and the control group. Effect sizes will be computed for the mean differences of the intervention and control arms at midpoint, endpoint, and follow-up.

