### Participant timeline {13}

The study will be implemented between May and August 2023. During this period, data will be collected within specified periods: at baseline (0 weeks into the study), midpoint (2 weeks into the study), endpoint (4 weeks into the study), and 1-month follow-up (8 weeks into the study) as shown in Table 1.

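### Adjustment for the baseline score is optional and its place in the model is undecided, so the arm-by-time test may forgo precision that data already planned would supply

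*Protocol article*

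**What the plan says.** All of the modelling text is in the Protocol article, section {20a} on statistical methods for the primary and secondary outcomes.

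- Fixed effects: "The arm, time, and interaction between these two will be included in all the models as fixed effects".
- Age, gender, lay provider, lay provider gender, school and county are to be included, each as a fixed or a random effect. The baseline score is treated differently: "Baseline scores may also be included". No rule says when.
- Random effects: "The standard models will be random-intercept models; we will also test the inclusion of random slopes for individual differences".
- Decision rule: a p-value below 0.05 "in the interaction between the time variable and the arm variable will be considered statistically significant". If it is met, arm differences are examined at each time from endpoint to follow-up. If it is not, a significant arm main effect can support the conclusion.

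Whether baseline is a row of the response is not stated. Three things suggest that it is. The section announces "Our data analysis plan will involve descriptive statistics, visualizations, and models of change over time". The abstract says that trajectories over time will be modelled, and "Outcomes will be assessed at baseline, midpoint (2 weeks), endpoint (4 weeks), and 1 month follow-up". Cohen's D is to be compared at baseline as well as at the later times.

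**The concern.** The baseline score of the same outcome is usually the strongest predictor of the later score, yet it is the only listed variable that the plan does not commit to. The choice matters in two ways.

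First, precision. If baseline is a response time and the arms have free means there, the arm-by-time interaction compares changes from baseline. That is less precise than a baseline-adjusted comparison whenever ρ is below 1. Using the option in that same model does not help the interaction, and it puts baseline on both sides of the equation.

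Second, meaning. With baseline as a response, the interaction asks whether the arms diverge from baseline. With post-baseline responses only, it asks whether the effect differs between midpoint, endpoint and follow-up, and a constant benefit moves into the arm main effect. The two-step decision rule therefore tests different things depending on a choice left open. This touches all five primary outcomes, and both the comparisons with treatment as usual and the centralized-versus-decentralized comparison.

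**Working it through.** **Inputs from the Protocol article, sections {14} on sample size and {16a} on sequence generation.** Standardized effect 0.22; α = 0.05 (two-sided assumed); power at least 80%; 1554 required and 1600 planned; attrition up to 30% at midpoint and endpoint and up to 40% at follow-up; three equal arms.

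**Assumed, because not given.** ρ of 0.4 to 0.7, equal between all pairs of times (as a random-intercept model implies); complete data among those retained; no clustering at first.

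**The plan's own figure.** Power = Φ(0.22/√(2f/n) − 1.96), with f = 1 for an unadjusted comparison at one time.
- 1554 × 0.6 / 3 = 310.8 per arm gives 78.3%.
- 1600 × 0.6 / 3 = 320 per arm gives 79.5%.

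The stated 80% is reproduced approximately. The simulation inputs are in a supplement that is not shown.

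**Variance factors f, in units of 2σ²/n.**
- Arm difference at one time, unadjusted: 1.
- Change from baseline (the interaction contrast): 2(1 − ρ).
- Baseline-adjusted, or constrained to a common baseline mean: 1 − ρ².

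Generalized least squares for a four-time random-intercept model gave the same three values. Adjustment therefore reduces variance by (1 − ρ)/2 relative to the change contrast and by ρ² relative to the single-time difference.

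| ρ | f, change | f, adjusted | Cut v change | Cut v single time | Power, change (n = 320) | Power, adjusted (n = 320) |
|---|---|---|---|---|---|---|
| 0.4 | 1.20 | 0.84 | 30% | 16% | 71.9% | 85.9% |
| 0.5 | 1.00 | 0.75 | 25% | 25% | 79.5% | 89.5% |
| 0.6 | 0.80 | 0.64 | 20% | 36% | 87.5% | 93.6% |
| 0.7 | 0.60 | 0.51 | 15% | 49% | 94.9% | 97.4% |

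The unadjusted single-time comparison has 79.5% power in every row. Over a wider range of ρ, 0.2 to 0.8, the cut runs from 40% to 10% for the change contrast and from 4% to 64% for the single-time difference. A variance cut of 15% to 30% is a standard-error cut of 1 − √0.85 = 8% to 1 − √0.70 = 16%.

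**Does using the option rescue the interaction?** Write the response of person i at time t as μ(t) + arm effect(t) + β·y(i,0) + u(i) + e(i,t). Subtracting the baseline row removes both β·y(i,0) and u(i), so a common-slope covariate drops out of every arm-by-time contrast. A simulated random-intercept model (320 per arm, four times, ρ = 0.5) agreed. The interaction estimate was the same with and without the covariate, and the standard error was 0.079 both times, which is √(2/320). The fitted slope averaged 0.62 instead of 0.50, because the baseline row has slope 1 on itself: (1 + 3 × 0.5)/4 = 0.625.

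For a single-time difference the option does help. With slope b, f = 1 + b² − 2bρ = 1 + 0.391 − 0.625 = 0.766, against 0.75 with the right slope.

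**Clustering.** Take about 7.5 retained per group (12.5 × 0.6) and an assumed intraclass correlation. The unadjusted factor is 7.5·ICC + (1 − ICC), and the adjusted factor is 7.5·ICC + (1 − ICC)(1 − ρ²). The single-time cut at ρ = 0.4 falls from 16% to 13.9% (ICC 0.02) or 11.5% (ICC 0.05). At ρ = 0.7 it falls from 49% to 42.5% or 35.1%.

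**Endpoint.** With 30% attrition, 1600 × 0.7 / 3 = 373 per arm. At ρ = 0.5 the change contrast has 85.2%. The adjusted contrast has Φ(0.22/√(1.5/373.3) − 1.96) = Φ(1.51) = 93.5%.

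**The case against.** The case against is substantial.

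- **Baseline as a response is inferred.** Nothing states it, and the fallback to an arm main effect reads more naturally if the rows are post-baseline. This stands, so the argument about the interaction is conditional on that reading.
- **The plan permits adjustment, so nothing need be lost.** This holds for single-time differences, and for a model with post-baseline rows only. It does not hold for the interaction test on the likelier reading, because the covariate cancels.
- **The final conclusion can rest on single-time differences, and the interaction is a joint test over times.** Correct. The change contrast above is one component of the first step, so both comparators are shown.
- **The power target is already about met.** Correct for an unadjusted single-time comparison without clustering. The point is forgone precision. For the change contrast, power falls clearly below 80% only when ρ is under about 0.5.
- **Covariate detail belongs in a statistical analysis plan.** Often so. Here the protocol takes up the matter and fixes it as optional, without saying which model it belongs to.

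A reader might also infer that the tests introduced with "To test for significant group differences in the sample characteristic variables" will decide whether baseline is adjusted for. They stand among the descriptive statistics, and nothing links them to covariate choice. That inference is not supported.

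**Conclusion.** The point holds in a limited form. Baseline adjustment is left optional without a rule, and the role of baseline in the model is undecided. If baseline is a response time, as the text suggests, the arm-by-time test is a change contrast that the optional covariate cannot improve, and single-time differences are unadjusted unless the option is used.

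The size rests on an assumed ρ. For ρ of 0.4 to 0.7, with complete data and no clustering, the variance reduction is 30% to 15% for the change contrast and 16% to 49% for a single-time difference. Clustering makes it smaller. The power gain at 320 per arm is about 14 points at ρ = 0.4 and under 3 points at ρ = 0.7.

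A reader might infer that the trial is certain to forfeit 15% to 30% of its precision. The documents do not support that: the option may be used, ρ is not reported, and the figure is a variance reduction for one contrast only. No bias is shown and no design change is needed. It is a worthwhile correction to make before analysis.

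**What to change.** Prespecify one model for all outcomes.

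(a) A constrained longitudinal model: baseline is a response, with one common mean across arms at baseline. The arm-by-time rule then keeps its meaning as a test of divergence from baseline.

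(b) Post-baseline responses only, with the same outcome's baseline score as a mandatory covariate and a baseline-by-time term. For academic performance the covariate is the preceding-term grade, and the during-term and after-term grades are the responses. The decision rule must then be reworded so that the conclusion rests on the adjusted arm differences at endpoint and follow-up (for grades, in the later terms), because the interaction would test only whether the effect varies after baseline.

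In either case, delete the sentence that makes baseline optional. Dropping the baseline significance tests is a matter of preference and not part of this correction.

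The cost is wording and process. The data are already in the collection schedule. Recruitment is reported as completed on July 14, 2023, so the change should be dated, made before outcomes are analysed, and communicated to the ethics board and registry as the amendment section {25} provides.

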### Sample size {14}

We used the *simr* package in R to estimate the sample size needed for this trial. We used the lowest standardized effect size between the intervention and control we observed in a prior study [8] as our target effects, which was 0.22. Power simulations revealed that to detect an effect size of at least 0.22 at any time point with a significance level of *α* = 0.05 and a power of at least 80%, an effective sample size (i.e., including attrition of 40%) of 1554 participants is required. We expect up to 30% attrition at the midpoint and endpoint and up to 40% by follow-up based on our past trial [8], which is high. We rounded this up to 1600 participants required at baseline. For more details on our sample size determination and power analysis procedure, please see the supplementary materials.

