## Assignment of interventions: allocation

### Sequence generation {16a}

Consenting students will be randomized into one of the three intervention arms using “ballot boxes.” Each supervisor will prepare a “ballot box” containing small pieces of paper which will indicate the group numbers and the intervention arm assigned. Participants will be invited to line up and pick a folded piece of paper from inside the ballot box, which will indicate their group number and allocated intervention. We aim to have equal numbers of students in each randomized group.

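### The protocol gives two criteria for concluding benefit that use different visits, and the model-based one does not say whether both later differences or only one must be significant

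*Protocol article*

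**What the plan says.** The statistical methods section for primary and secondary outcomes {20a} sets out a model rule in two steps. First the arm-by-time interaction is tested at 0.05. If it is significant, "we will look at the conditional mean difference between the arms at each time point from end point to follow-up". Improvement is concluded if these differences are significant and the control arm does worse. If the interaction is not significant, a significant main effect of an active arm in the favourable direction is enough.

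The next paragraph adds a second criterion. Cohen's D is compared "for each outcome at baseline, midpoint, endpoint, and 1-month follow-up for the study participants", and a statistically significant D in the favourable direction is said to reflect greater improvement than control.

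Two other places name visits. The sample size section {14} bases the number of participants on power "to detect an effect size of at least 0.22 at any time point with a significance level of" 0.05. The abstract says effect sizes will be computed for the "mean differences of the intervention and control arms at midpoint, endpoint, and follow-up".

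**The concern.** The two criteria in {20a} do not cover the same visits. The model contrasts that support a claim are at endpoint and follow-up. The Cohen's D sentence also covers midpoint and baseline, and its wording is inferential: a significant value is read as improvement. At baseline no treatment effect can exist, so a significant D there is chance imbalance.

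Within the model rule, the text does not say whether the endpoint and follow-up differences must both be significant or whether one is enough. A difference at only one of the two visits passes or fails on that reading.

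At stake is what may be concluded. The same data can give improvement by one sentence and no improvement by the next, for each questionnaire outcome and each active arm. If this stays open, the criterion can be chosen after the results are known.

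**Working it through.** **Inputs from the protocol.** Effect size 0.22, "with a significance level of *α* = 0.05 and a power of at least 80"% (sample size section). Total: "an effective sample size (i.e., including attrition of 40%) of 1554 participants is required", rounded up to 1600. Attrition: "We expect up to 30% attrition at the midpoint and endpoint and up to 40% by follow-up". Allocation: "We aim to have equal numbers of students in each randomized group", taken as 1:1:1.

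**Assumptions, not in the protocol.** Two-sided tests, SD 1, no clustering, equal correlation between visits of 0.3 to 0.7.

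**The plan's own figure.** Sample size per arm for one two-arm contrast: n = 2(1.960 + 0.842)²/0.22² = 324.3, so 325. Three arms need 975, and 975/0.60 = 1625, which is 4.6% above 1554. Exact agreement is not expected, because the figure came from a simulation whose inputs are in a supplement that is not shown.

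In the other direction, power = Φ(0.22·√(n/2) − 1.960):

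- Follow-up, N = 1554: n = 1554/3 × 0.60 = 310.8, power 78.3%.
- Follow-up, N = 1600: n = 320, power 79.5%.
- Midpoint or endpoint, N = 1600: n = 1600/3 × 0.70 = 373.3, power 85.2%.

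So the stated 80% is close to the power of one arm-versus-TAU contrast at the visit with most attrition.

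**The two criteria compared.** I simulated the arm-by-visit mean estimates at N = 1600 (200,000 draws per scenario, three arms, four visits, the stated attrition as monotone dropout, both active arms sharing the effect). The covariance is that of a likelihood-based model using all available data. The model rule is: 6-df interaction test significant and the later difference(s) significant in the favourable direction; or interaction not significant and the arm effect averaged over visits significant. The D criterion is: at least one favourable significant difference among the four listed visits. Results for one outcome and one active arm, over correlations 0.3 to 0.7:

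| True effect | Some significant favourable D | Model rule, both needed | Model rule, either enough |
|---|---|---|---|
| None | 7.1–8.9% | 2.3–2.5% | 2.9–3.1% |
| 0.22 at midpoint only | 86–90% | 0.8–4.5% | 4.4–8.1% |
| 0.22 at midpoint, endpoint and follow-up | 97–99% | 77–83% | 95.1–95.8% |

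The nominal rate for one favourable two-sided test is 2.5%. Dropping only baseline from the D criterion still leaves 5.8–6.9% under no effect.

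**Sensitivity.** If each visit is analysed on its available cases, with no gain from the other visits, the midpoint-only effect is claimed in about 85% by D and again in at most 8% by the model rule. For the sustained effect the model rule then has about 74–75% power (both) or 91–95% (either). Clustering would lower the power figures further.

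**The case against.** Several stronger readings are tempting, and the document does not support them.

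- A reader might count four definitions of benefit. The abstract only lists visits at which effect sizes are computed, and the sample size section states power. Claim criteria appear only in {20a}, and there are two.
- A reader might infer that the analysis ignores the midpoint. Only the follow-on contrasts skip it. The interaction test and the main-effect fallback are not restricted to later visits, and the Cohen's D sentence names the midpoint. The simulation includes the interaction test and the fallback, and the midpoint-only effect is still rarely claimed by the model rule.
- A reader might infer that the 80% power is wrong. Power at any time point may mean at each visit taken singly, which covers endpoint and follow-up. The simulation inputs are not shown. For a sustained effect the full rule gives roughly 80% even if both differences are needed, and more if either is enough.
- A reader might want the interaction test removed. The abstract states the aim as trajectories over time, for which an interaction test followed by visit contrasts is conventional. Removing it is a design preference.

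It can also be said that an effect confined to the midpoint, after two of four sessions, is unlikely, and that nobody would present a baseline difference as benefit. Both are fair. Visit-level detail is also often left to an analysis plan. What remains is that this section does state its criteria, and they conflict as written. The excess of significant D values under no effect does not depend on an unlikely effect pattern.

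**Conclusion.** The point holds as an inconsistency between two stated benefit criteria, together with an unresolved reading inside one of them. It should be corrected.

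The conflict over visits is plain from the text and needs no assumption. Its size rests on visit correlations of 0.3 to 0.7, independence between participants and the stated attrition. For a midpoint-only 0.22 effect, the two criteria differ by nearly 80 percentage points or more. Under no effect, the D criterion gives about three times the nominal 2.5% favourable rate per outcome and arm. For a sustained effect, the both-or-either reading moves power by about 13 to 19 points (by about 17 to 20 on available cases). No error in the stated sample size or power is shown. The figures concern the questionnaire outcomes; academic performance is measured by school term and does not follow these visits.

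**What to change.** In the statistical methods section {20a}:

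- Make the mixed-model arm-versus-TAU contrast at named post-treatment visit(s) the only basis for a claim on the questionnaire outcomes. Either name endpoint as the deciding visit, or keep endpoint and follow-up and say whether both or either must be significant.
- Make Cohen's D descriptive, and remove baseline and midpoint from the sentence that reads a significant D as improvement.

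In the sample size section {14}, replace the reference to any time point with the power for the named contrast or rule.

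The cost is a few sentences and a rerun of the existing simulation for that contrast; no further data collection is required. The downside is that an effect seen only at another visit becomes supportive evidence and no longer carries a claim. If both later differences are to be required, the rerun should show whether 1600 still gives the intended power once clustering is included.
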